### 4.4. Imaging Assessments

Imaging is performed on a Siemens Prisma 3T MRI with a standard 20 channel head-neck array coil (Siemens Healthineers, Erlangen, Germany). T1 weighted MPRAGE images at 1 mm isotropic resolution are acquired to determine lesion location and volume. Lesion location is categorized as involving the posterior limb of the internal capsule (PLIC), other subcortical structures, and/or cortices.

Diffusion tensor imaging (DTI) is also performed to assess white matter integrity of corticospinal tracts (27). A high angular resolution diffusion imaging (HARDI) sequence is acquired at 2 mm isotropic resolution. A unit-less measure of tissue integrity, Fractional anisotropy (FA) is measured at the level PLIC because it represents a major convergence point for corticospinal tracts (28) and is predictive of motor impairment, and functional gains (29).

## 5. Data and Safety Monitoring

A separate Trial Operations Committee monitors ethical and regulatory aspects, scientific integrity and fiscal integrity of the trial. An independent medical monitor (stroke neurologist) is assigned to the trial. The monitor reviews the study data, evaluates treatments for adverse events, judges whether the overall integrity and conduct of the study remain acceptable, and makes recommendations to the Trial Operations Committee. A quarterly review is performed to update the committee on progress of the trial, review enrollment, dropouts, data collection, and safety (adverse events). All adverse events are reported to the local IRB and categorized as serious/not serious, related/not related, and expected/unexpected. All staff associated with the study are required to complete human subject research training through the Cleveland Clinic and similar NIH programs.

## 6. Sample Size Determination

The estimated CCFES + Sham rTMS vs. CCFES + cHMC facilitation effect size is 0.87, calculated from common standard deviation from our previous studies, 6 (2), with expectation of a between-group difference of UEFM, 5.2 [minimal clinically important difference, MCID (3)]. With this effect size, a type I error of 0.05 and power of 80%, 22 subjects are needed per group. With an expected attrition rate of 10%, 72 is the planned sample size to ensure 22 per group to complete the study.

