## 2. Methods

### 2.1. Participants

This study is a randomized, sham-controlled, and double-blinded clinical trial of up to 72 participants who had suffered a stroke at least 6 months previously and who continue to experience severe chronic upper limb motor impairment. Clinical assessment of the motor impairment is performed by an occupational therapist. “Severe” motor deficit is being defined as the inability to extend wrist ≥10-degrees, extend/abduct thumb ≥10-degrees, or extend two other digits ≥10-degrees (exclusion criteria in CIMT studies). This clinical motor criterion was chosen because it has a better prospect of being generalizable and was also used to define “severe” motor impairment in the previous CCFES clinical trial (2). Participants are required to have functional paretic hand opening in response to neuromuscular electrical stimulation of finger or thumb extensors to ensure it is feasible for them to undergo CCFES-mediated rehabilitation (See Inclusion Criteria, Table 1). Participants are excluded for contraindications to TMS and magnetic resonance imaging (MRI), including cardiac pacemaker, history of seizures, substance abuse, metallic implant in the head etc. determined by a stroke neurologist (See Exclusion Criteria, Table 2). Participants are being recruited from the Cleveland Clinic, Cleveland, OH. The trial is governed by human research protection policies of the Cleveland Clinic Institutional Review Board. All participants provide written informed consent before participating.

**Table 1 T1:** Inclusion criteria.

• Age 18–90 years old at the time of randomization
• >6 months since a first clinical cortical or subcortical, ischemic or hemorrhagic stroke
• Severe upper limb hemiparesis defined as lacking ≥10-degrees active wrist extension or ≥10-degrees active thumb abduction/extension or ≥10-degrees active extension in at least two additional digits (i.e., will not meet minimum constraint induced movement therapy criteria)
• Memory of at least 2 out of 3 items after 30 min
• Able to perform 3-stage command
• Full volitional hand opening/closing of the non-paretic hand
• Ability to follow instructions for putting on and operating the contralaterally controlled functional electrical stimulation (CCFES) device or have a caregiver available to provide assistance

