### 2.2. Randomization

Participants are assigned to one of three treatment groups—CCFES plus 5 Hz rTMS of cHMC, CCFES plus 5 Hz rTMS of iM1, or CCFES plus sham rTMS of cHMC/iM1 using an adaptive randomization algorithm (14, 15). The algorithm is designed to minimize group imbalances on 4 key participant characteristics: (1) time post-stroke (<2 years vs. ≥2 years), (2) presence of cortical vs. subcortical lesion, (3) presence of active wrist extension vs. none and (4) paresis of dominant vs. non-dominant side. Two years post-stroke was chosen as stratification cutoff because our previous CCFES trial had reported a higher likelihood of response in participants within that time-frame (2). With the inclusion of the wrist extension, we expect that baseline differences in degree of distal upper limb severity will be minimized. Balancing across the three groups can still be challenging. Allocation is concealed by storing group assignments in a binder to which only the study coordinator and rTMS interventionists have access.

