## 7. Statistical Analysis

All statistical analyses will be performed using the intent-to-treat principle, comparing outcomes by the assigned groups (linear mixed model analysis). The primary endpoint will be change in UEFM score from baseline to end-of-treatment at 12 weeks. Changes in UEFM, WMFT-rate, SIS-16 and neurophysiologic metrics will be modeled using a linear mixed effects approach, which is well-suited for handling correlated repeated measurements, unbalanced data, missing data and dropouts and also permits us to control for potential confounders (30). As secondary analysis, “responders” will be identified among the three groups, with response defined as the attainment of ≥4.25 point-gain on the UEFM (3). As secondary analysis, “responders” will be identified among the three groups, with response defined as the attainment of ≥4.25 point-gain on the UEFM (3).

The adjusted least square mean estimates from the linear mixed effects models will be used to compare the effectiveness of the CCFES + cHMC rTMS to CCFES + iM1 rTMS, and CCFES + sham (**Hyp 1**). Linear regression models will be used to evaluate the association between changes in neurophysiologic and motor outcomes (**Hyp 2**). Separate regression models will be used to determine if treatment response is associated with baseline impairment, lesion size/location and corticospinal damage (**Hyp 3**).

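### At the stated 10% attrition, 72 participants give an expected 64.8 completers (21.6 per group), slightly short of the 22 per group that 72 is said to secure

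*Protocol article*

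**What the plan says.** Section 6 (Sample Size Determination) of the protocol article builds the number in two steps.

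- **Requirement per group.** It takes "The estimated CCFES + Sham rTMS vs. CCFES + cHMC facilitation effect size is 0.87", obtained from a common SD of 6 UEFM points and "with expectation of a between-group difference of UEFM, 5.2". It then states: "a type I error of 0.05 and power of 80%, 22 subjects are needed per group".
- **Allowance for loss.** "With an expected attrition rate of 10%, 72 is the planned sample size to ensure 22 per group to complete the study".

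Section 2.2 (Randomization) gives the number of groups: "Participants are assigned to one of three treatment groups". No allocation ratio is stated. Section 2.1 (Participants) words the total as a maximum: "double-blinded clinical trial of up to 72 participants". Section 7 (Statistical Analysis) plans an intent-to-treat linear mixed model, described as "well-suited for handling correlated repeated measurements, unbalanced data, missing data and dropouts".

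**The concern.** The second step does not follow from its own inputs. If 22 per group must finish and one participant in ten is expected to leave, 24 per group is not quite enough: the expected number finishing is below 22. The word *ensure* makes the mismatch plainer, because it presents as secured a count that lies above the expected value.

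Readers use the completer target and the power attached to it to judge what a null result means. Someone who later compares actual retention with the plan should find that enrolment, attrition and completers fit together. Here, a trial that met its enrolment and attrition assumptions exactly would still be expected to miss its completer target. The amount at stake is about one participant across three arms, so this concerns the accuracy of a stated figure and leaves the design untouched.

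**Working it through.** **Inputs.** From section 6: difference 5.2, SD 6, effect size 0.87, type I error 0.05, power 80%, 22 per group, attrition 10%, total 72. From section 2.2: three groups. Assumed because the article does not state them: a two-sided two-sample t test, and equal allocation (24 per group).

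**1. Reproduce the 22 per group.**
- Effect size: 5.2 / 6 = 0.8667, stated as 0.87.
- Power of a two-sided t test with n per group: noncentrality d × √(n/2), on 2n − 2 degrees of freedom.
- At n = 22, power is 80.2% (d = 5.2/6) or 80.5% (d = 0.87). At n = 21 it is 78.2% or 78.5%.
- The smallest n reaching 80% is therefore 22, as stated. The normal approximation would give 21 and a one-sided version of it 17, so the two-sided t test is the calculation that matches the article.

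**2. Completers needed.** 3 × 22 = 66.

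**3. Completers expected from 72 at 10% attrition.**
- Total: 72 × 0.90 = 64.8, which is 66 − 64.8 = 1.2 short.
- Per group: 24 × 0.90 = 21.6, which is 0.4 short.

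**4. Enrolment that 10% attrition would require.**
- Whole trial: 66 / 0.90 = 73.3, so 74.
- By group: 22 / 0.90 = 24.4, so 25 per group and 75 in total.
- The looser rule of adding 10% also exceeds 72: 66 × 1.10 = 72.6, so 73.

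**5. Attrition that 72 does allow.** (72 − 66) / 72 = 6 / 72 = 8.3%, or 2 participants per group.

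**6. Effect on power, completers only, two-sided t test.**

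| Completers per group | d = 5.2/6 | d = 0.87 |
|---|---|---|
| 22 | 80.2% | 80.5% |
| 21.6 | 79.4% | 79.7% |
| 21 and 22 | 79.2% | 79.5% |
| 21 | 78.2% | 78.5% |

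Moving from 22 to 21.6 per group costs 0.8 points. By the normal approximation, power at 21.6 is 81.3% to 81.6%, but that method is not the one that yields 22.

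**The case against.** The strongest reply is that this is rounding. A count of 21.6 rounds to 22, 72 is within two of the strict figure of 74, and 79.7% at the stated effect size rounds to 80%. That is right about the consequence. It does not make the sentence correct: a required minimum is not met by rounding an expected count upward, and no usual rule that rounds up turns 66 and 10% into 72.

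A reader might go further and infer that the trial fails to deliver its 80% power. The documents do not support that, for three reasons.

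- **The attrition concerns completing the study.** Assessments run to week 36, while the primary endpoint is the UEFM change at week 12. If the 10% covers the whole period, some of it may fall after the endpoint, and fewer than 10% may be missing from the primary comparison.
- **The planned analysis is not a completers-only t test.** Section 7 specifies a mixed model that can use partial data, and UEFM is also measured at week 6 (Table 3). A participant lost between weeks 6 and 12 still contributes.
- **The test and its sidedness are not named**, so the sub-80% figures depend on the t-test assumption.

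A reader might also argue from chance variation in losses. With 24 per arm and independent 10% loss, an arm keeps at least 22 with probability 56%, and all three do so with probability 0.564³ = 18%. This does not single out 72. With 25 per arm the figures are 76% and 45%, so correctly inflated enrolment would not guarantee 22 per group either. Inflation for dropout conventionally targets the expected count. The argument supports softening *ensure*, but it does not show that 72 is inadequate. Nor does the maximum of 72 in section 2.1 change the arithmetic.

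**Conclusion.** The point holds as a minor inconsistency. The article's own figures give 64.8 expected completers against the 66 it says 72 will secure: 1.2 short in total and 0.4 short per group. Nothing elsewhere in the article reconciles them. The total shortfall needs only the three stated numbers and the number of groups. The per-group figure also assumes equal allocation.

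The consequence for power is under one point on a completers-only two-sided t test, and the mixed model and the timing of losses may offset it. The finding therefore does not establish that the trial is underpowered, and it gives no reason to enlarge it.

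**What to change.** Keep 72 and correct the sentence in section 6 in one of two ways:

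- *72 enrolled (24 per group) allows for about 8% attrition (2 per group) while retaining 22 per group*; or
- *with 10% attrition, about 65 participants are expected to complete (21 to 22 per group), giving power just under 80% by a two-sample t test for cHMC versus sham.*

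In either case, describe the completer count as expected instead of ensured. If the second wording is used, name the t test as the basis, so that the figure is not read as the power of the planned mixed model. The cost is one sentence and, under the second option, a marginally less favourable power statement. Participant numbers, design and analysis stay as they are.

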## 7. Statistical Analysis

All statistical analyses will be performed using the intent-to-treat principle, comparing outcomes by the assigned groups (linear mixed model analysis). The primary endpoint will be change in UEFM score from baseline to end-of-treatment at 12 weeks. Changes in UEFM, WMFT-rate, SIS-16 and neurophysiologic metrics will be modeled using a linear mixed effects approach, which is well-suited for handling correlated repeated measurements, unbalanced data, missing data and dropouts and also permits us to control for potential confounders (30). As secondary analysis, “responders” will be identified among the three groups, with response defined as the attainment of ≥4.25 point-gain on the UEFM (3). As secondary analysis, “responders” will be identified among the three groups, with response defined as the attainment of ≥4.25 point-gain on the UEFM (3).

The adjusted least square mean estimates from the linear mixed effects models will be used to compare the effectiveness of the CCFES + cHMC rTMS to CCFES + iM1 rTMS, and CCFES + sham (**Hyp 1**). Linear regression models will be used to evaluate the association between changes in neurophysiologic and motor outcomes (**Hyp 2**). Separate regression models will be used to determine if treatment response is associated with baseline impairment, lesion size/location and corticospinal damage (**Hyp 3**).

## 8. Discussion

Our ongoing clinical trial represents the first to investigate the effects of multiple sessions (22 sessions over 12 weeks) of CCFES-mediated therapy combined with rTMS facilitation of the contralesional higher motor cortices (cHMC) in chronic stroke survivors with severe hand impairment. Up until now, the effects of this novel approach have been only evaluated in single sessions (11, 13). The anticipation is that multiple sessions over several weeks would be beneficial for return of motor function in a population that requires longer and more intense training for motor improvement.

CHMC make positive contributions to paretic limb movement in the absence of sufficient ipsilesional pathways and is also specialized for bilateral movements (8–10). So, we hypothesize that combining CCFES-based therapy, which involves simultaneous opening and closing of both hands, with facilitation of cHMC will produce greater gains in motor recovery in stroke survivors with severe hand impairment than combining CCFES with facilitation of iM1 or sham brain stimulation. Superior effects of combining CCFES with cHMC-facilitation would validate our hypothesis that cHMC is a suitable target to promote motor function in the more severely impaired population (**Hyp 1**). If gains in motor function are achieved with CCFES + facilitation of cHMC and these gains are associated with increases in excitability of uncrossed pathways and rebalanced IHI, this would provide evidence of neuroplastic mechanisms specific to behavioral restitution for persons with more severe motor impairment (**Hyp 2**). Identifying which recovery phenotypes are associated with a favorable response (**Hyp 3**) would help identify biomarkers to select the best candidates for future larger efficacy trials.

Identifying the value of any approach that is specific to promoting motor function in stroke survivors with severe neurological damage and motor impairment potentially has far-reaching impact. After all, these individuals typically have limited opportunities for significant recovery, and treatments commonly given in clinics or tested in research are not feasible to make available to them (generally because criterion level of movement required is lacking). By including those stroke survivors who otherwise have too severe of a hand impairment to qualify for evidence-based therapies like CIMT, we seek to generalize the use of a potentially promising approach like brain stimulation. Instead of using a brain stimulation approach that is contingent upon the presence of residual ipsilesional pathways (iM1 facilitation), we propose here the use of a novel approach that relies on targeting what is intact in persons with severe (unilateral) ipsilesional damage. In this way, we seek to capitalize on “what remains” and not “what once was”, a critical step in developing targeted treatments.

Several safeguards are included to ensure the scientific rigor, reproducibility, and transparency of our findings. These include: inclusion of a homogeneous sample of more severe participants based on a clinical criterion (lack of minimal extension at fingers/wrist) for improving the statistical power of detecting between-group differences; application of CCFES in all groups with one of the groups receiving sham rTMS to differentiate the gains achieved by CCFES alone; multiple, assessor-blinded assessments performed before, during and after the end of the intervention to capture trends of motor improvement and retention of those effects for 6 months; and inclusion of baseline lesion characteristics, demographic and neurologic data, and treatment adherence in analytic models to improve variance in treatment effects.

## 9. Summary and Conclusions

We hypothesize that the combination of CCFES with rTMS facilitation of cHMC will produce greater reduction in motor impairment and perceived disability, and larger gains in functional ability compared to CCFES with rTMS facilitation of iM1 and CCFES with sham rTMS. Findings in line with our hypothesis would reveal that intact contralesional regions make more significant contributions to movement recovery than damaged ipsilesional regions in chronic stroke survivors with severe damage and impairment.

## Ethics Statement

The studies involving human participants were reviewed and approved by Cleveland Clinic Institutional Review Board. The patients/participants provided their written informed consent to participate in this study.

